### Data

#### Collection and management

The study will be conducted in accordance with Good Clinical Practice and the Data Protection Act 2018. Cognitive and motor data will be collected on hard-copy scoring sheets and electronically via PEBL [90] and PsychoPy [81] on a computer in a quiet testing laboratory at CUBRIC. Behavioural data collected using hard-copy scoring sheets will be stored in a locked cupboard in an access-restricted office in CUBRIC. Q-MedX software will automatically capture Q-Motor data, which will be stored on a password-protected laptop.

Behavioural data from PsychoPy tests will be cleaned by removing practice trials and extreme or outlier values, and subsequently analysed using R statistical software. Extreme values and outliers (scores > 3 standard deviations ± the mean) will be identified using the rstatix R package [91] and will be reported and excluded where appropriate.

MRI data will be collected according to CUBRIC standard operating procedures (SOP) including MRI safety and operation guidelines by trained MR operators. MRI data will be acquired on the Siemens 3 Tesla Connectom system at CUBRIC and stored on the XNAT system.

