### Secondary objectives

To obtain estimates of variability and absolute change pre- and post-training compared to usual activity in the following measures:Performance scores in cognitive and motor assessments for future RCT sample size calculations.Grey and white matter microstructure means in basal ganglia and cerebellar networks and auditory networks to investigate possible neural mechanisms that may underpin cognitive training effects

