Stroop test	The Stroop test measures the ability to ignore response interference. A computerised version of the Stroop test will be administered via PsychoPy [81]. Colour words are presented in ink which is either congruous (e.g., the word “blue” printed in blue ink) or incongruous (e.g., the word “blue” printed in red ink). Depending on instructions, participants must either respond to the colour meaning of the word or the colour ink in which it is written. Two practice blocks of 24 trials will be presented before two experimental blocks of 72 trials
Digit span (forward and backward) [80]	A random sequence of numbers is read aloud to participants and they must recall the numbers either forwards or backwards, depending on the trial. Number of correctly recalled numbers is taken as a measure of working memory capacity. The test is discontinued if a participant answers two sequential trials of the same number of items incorrectly
N-Back	The *N-*back involves the continuous presentation of a series of stimuli (e.g., letters). The participants must indicate whether the current stimulus is the same as *N* steps earlier in the sequence [82]. Number of correct responses versus false alarms and misses is a measure of updating working memory. The *N*-back will be administered on the Psychology Experiment Building Language (PEBL; 82). Participants will respond to a sequence of letters, then to spatial location of squares on a grid. A dual-task block of trials will also be included where participants must respond to both letters and squares
Trail-Making Test (TMT; [32])	The TMT consists of two parts: A and B. Part A measures visual attention. Participants are instructed to join numbered circles from 1–25 in ascending order as quickly as possible. Part B measures attention-switching, Participants must alternate between joining numbers and letters (1-A-2-B etc.) as quickly as possible. Performance is measured by completion times for both parts. The TMT is highly correlated (0.72–0.80) with other measures such as the Wechsler Adult Intelligence Scale – III [83], indicating excellent construct validity. Inter-rater reliability for TMT is also high (*r* = -.96)

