#### Sample size

In line with the Consolidated Standards of Reporting Trials (CONSORT) statement extension for randomised pilot and feasibility trials [89], formal power calculations have not been performed. We plan to recruit 50 cognitively healthy individuals from the local area, a target chosen pragmatically based on the required level of participant engagement and available resources. This sample size will enable estimation of recruitment, retention, and adherence rates within a 95% binomial confidence interval, with a margin of error of no more than ± 15 percentage points, regardless of point estimate.

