#### Statistical methods

The study will be reported in line with CONSORT reporting requirements for pilot and feasibility trials [89]. Since this is a feasibility trial, it is not formally powered to test for effectiveness of the intervention whilst controlling for type 1 error. The primary purpose of the trial is to assess the feasibility, by measuring recruitment, retention and adherence rates and acceptability scores of the intervention. Feasibility percentage rates will be calculated as follows:Recruitment rate = 100 x (number of participants who provided consent/number of participants eligible) %Retention rate = 100 x (number of participants who complete follow-up testing/number of participants who provided consent)Adherence rate (frequency) = 100 x (number of days’ practice logged/40 days) %Adherence rate (duration) = 100 x (number of minutes practice logged/(40 days × 30 min average session duration = 1,200 min) %

Descriptive statistics (means and standard deviations) of effect sizes and 95% confidence intervals will be calculated for all secondary outcome measures, listed in Table 2. Mean and standard deviation of participants’ absolute and percentage changes from baseline will be computed to quantify effect sizes and variability in performance in the two groups.

With regard to our secondary outcome measures, which concern cognitive and motor abilities and estimates of underlying grey and white matter microstructure, the following exploratory analyses will be carried out. Because this is a feasibility study, these planned analyses are intended to generate hypotheses about how music training may stimulate cognitive and motor networks, rather than being fully-powered to determine training efficacy. Independent *t-*tests will be conducted on TICS, age, years of musical experience and musical aptitude (measured using the micro-PROMS, see Table 2 for further details) to determine any significant differences between piano and control groups at baseline, which could influence the effects of the training. To investigate the effect of piano training on cognitive and motor outcome measures and neuroplasticity, linear mixed models will be conducted in R using the lme4 package [92], with group, time and baseline measures as covariates variables. Statistical methods for handling missing data will be reported if required.

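### Removing scores beyond 3 SD lowers the variability estimates that the trial is meant to supply for planning, and the exclusion decision is discretionary with no stated blinding to arm

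*Protocol article*

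**What the plan says.** Under Collection and management, the protocol article states: "Behavioural data from PsychoPy tests will be cleaned by removing practice trials and extreme or outlier values". The next sentence sets the threshold and the tool, "Extreme values and outliers (scores > 3 standard deviations ± the mean) will be identified using the rstatix R package", and says that such values "will be reported and excluded where appropriate". Removal is therefore unconditional in one sentence and a matter of judgement in the next. Table 2 names one PsychoPy test: "A computerised version of the Stroop test will be administered via PsychoPy".

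Two other places make spread a deliverable of the trial. The secondary objectives begin "To obtain estimates of variability and absolute change pre- and post-training compared to usual activity" and name the first use: "Performance scores in cognitive and motor assessments for future RCT sample size calculations". Under Statistical methods, the mean and SD of absolute and percentage change from baseline are to be computed "to quantify effect sizes and variability in performance in the two groups".

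On size: "We plan to recruit 50 cognitively healthy individuals from the local area", allocated equally, so about 25 per arm. The one sensitivity analysis described (Group allocation) concerns unblinded follow-up assessments, not outlier exclusions.

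**The concern.** The trial promises an SD to the planners of the next trial, and the cleaning rule works directly on that SD. An extreme but valid score belongs to the population that the future RCT will enrol. Removing it because it is extreme makes the population look more uniform than it is, and a sample size built on the reduced SD is too small.

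The second issue is judgement. The paragraph gives no criterion for when exclusion is appropriate and does not say that the decision is taken without sight of arm. The trial is labelled unblinded, and the author who implements randomisation also enters and checks the scores (Group allocation; Monitoring). With about 25 per arm, one or two discretionary removals can move a group mean.

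**Working it through.** The plan gives no figure for the effect of its rule, so there is none to reproduce.

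**Step 1: direction and size of a single exclusion.** If one score lies z SDs from the mean of n scores, the variance without it, relative to the variance with it, is

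[(n − 1) − n·z²/(n − 1)] / (n − 2).

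At z = 3:
- n = 25: (24 − 9.375)/23 = 0.64
- n = 50: (49 − 9.184)/48 = 0.83

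A score further out gives a smaller ratio. So whenever the rule removes a single score, the reported variance drops by at least 36% (n = 25) or 17% (n = 50), whatever the distribution. This is not the bias, because a sample that contains an extreme score tends to have a high SD to begin with. The bias is the average over all samples.

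**Step 2: average loss.** Simulation with 40,000 samples per cell and one pass of the 3 SD rule. The entry is mean variance after the rule divided by mean variance before it. Shapes and pre-post correlations are assumptions; the documents give none.

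| Assumed shape | Change score, n = 25 (correlation 0.7 to 0.85) | Raw score, n = 25 | Raw score, n = 50 |
|---|---|---|---|
| Normal | 0.99 | 0.991 | 0.983 |
| Log-normal, log-SD 0.2 | 0.975 | not run | not run |
| Log-normal, log-SD 0.3 | 0.95 | 0.917 | 0.887 |
| t, 5 df | not run | 0.869 | 0.836 |
| Normal, 5% of values at triple SD | not run | 0.832 | 0.800 |
| Log-normal, log-SD 0.5 | 0.84 to 0.85 | 0.797 | 0.761 |

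The change-score column matches the quantity that Statistical methods promises by group: losses of about 1%, 2.5%, 5% and 15 to 16%. The 24% loss appears only for raw scores pooled over both arms with strong skew (or with t on 4 df, ratio 0.764).

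**Step 3: what this does to the future trial.** Take d = 0.39, the meta-analytic effect on inhibitory control cited in the Introduction, with two-sided alpha 0.05 and 80% power (both assumed). Then

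n per arm = 2(1.960 + 0.842)²/0.39² = 103.2, rounded up to 104.

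Planned n scales with the variance. True power is Φ(0.39·√(n/2) − 1.960).

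| Variance ratio | Planned n per arm | True power |
|---|---|---|
| 0.99 | 103 | 79.9% |
| 0.95 | 99 | 78.3% |
| 0.85 | 88 | 73.5% |
| 0.76 | 79 | 68.8% |

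**Step 4: the single-trial reading.** If the rule trims single Stroop responses within a person, the effect on between-person spread is different. With 144 experimental trials (two blocks of 72), log-normal times, between-person log-SD 0.2 and within-person log-SD 0.3 (both assumed), the variance of participants' mean scores falls by about 2%.

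**The case against.** The strongest reply is that the rule is narrower and its effect smaller than it first appears. The paragraph opens with PsychoPy data, and Stroop is the only test stated to run there: N-back runs in PEBL, digit-symbol is on paper and Q-Motor has its own software. Outliers are listed beside practice trials, which makes a single-trial reading plausible, and Step 4 shows that reading does little harm. Many outcomes are counts of correct responses or words, for which a loss near 1% is the more relevant figure. Sampling error is larger than most of these biases: an SD on 24 df has a 95% interval of roughly 0.78 to 1.39 times its value. Exclusions will be reported, the primary feasibility outcomes are untouched, and the group comparisons are exploratory.

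Most of this stands, and it limits the size of the point. It does not remove it. The threshold sentence speaks of scores, not responses. Even on the narrowest reading it covers Stroop, which is named in the secondary hypotheses and falls under the planning objective. Sampling error goes in both directions, whereas this bias always lowers the SD. Reporting exclusions does not commit the trial to giving the SDs with all scores kept.

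A reader might also infer that the exclusions will be made by someone who knows the arms. The documents do not say so: they name neither the analyst nor the person who decides. The overlap of roles makes it possible, but the supportable statement is only that no blinding of this decision is stated. Nor does the text remove participants; it removes values.

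**Conclusion.** The point holds as a conflict between a stated cleaning rule and a stated objective, with modest size for most outcomes. If the rule is applied to participant-level scores, the variance of change at 25 per arm is understated by about 1% for normal scores, 2.5 to 5% with mild skew and about 15% with strong skew. At the last figure, the illustrative future trial would have about 73% power instead of 80%, provided its planners use the trimmed SD unadjusted.

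It would be tempting to say that the future sample will be a quarter too small. That rests on strongly skewed or heavy-tailed raw scores pooled at 50, which is the top of the range and not the quantity promised by group; nothing in the documents supports that shape for the outcomes in general. Reach beyond the PsychoPy data is likewise unproven.

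Discretionary exclusion could also shift the group difference. Because those comparisons are hypothesis-generating, no confirmatory conclusion is at risk.

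**What to change.** Replace the two cleaning sentences with a rule that does the following:

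- Keeps all valid participant-level scores in the main analysis and in the SDs reported for planning. Only documented invalid measurements are excluded, judged without sight of arm.
- Limits outlier trimming to single trials of computerised tasks, under a prespecified rule that names the tasks.
- Reports the 3 SD exclusion of participant-level scores as a sensitivity analysis, with SDs shown with and without exclusions.

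The cost is a few sentences, slightly larger reported SDs and one extra analysis. Legitimate removal of failed or invalid recordings is preserved.

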#### Statistical methods

The study will be reported in line with CONSORT reporting requirements for pilot and feasibility trials [89]. Since this is a feasibility trial, it is not formally powered to test for effectiveness of the intervention whilst controlling for type 1 error. The primary purpose of the trial is to assess the feasibility, by measuring recruitment, retention and adherence rates and acceptability scores of the intervention. Feasibility percentage rates will be calculated as follows:Recruitment rate = 100 x (number of participants who provided consent/number of participants eligible) %Retention rate = 100 x (number of participants who complete follow-up testing/number of participants who provided consent)Adherence rate (frequency) = 100 x (number of days’ practice logged/40 days) %Adherence rate (duration) = 100 x (number of minutes practice logged/(40 days × 30 min average session duration = 1,200 min) %

Descriptive statistics (means and standard deviations) of effect sizes and 95% confidence intervals will be calculated for all secondary outcome measures, listed in Table 2. Mean and standard deviation of participants’ absolute and percentage changes from baseline will be computed to quantify effect sizes and variability in performance in the two groups.

With regard to our secondary outcome measures, which concern cognitive and motor abilities and estimates of underlying grey and white matter microstructure, the following exploratory analyses will be carried out. Because this is a feasibility study, these planned analyses are intended to generate hypotheses about how music training may stimulate cognitive and motor networks, rather than being fully-powered to determine training efficacy. Independent *t-*tests will be conducted on TICS, age, years of musical experience and musical aptitude (measured using the micro-PROMS, see Table 2 for further details) to determine any significant differences between piano and control groups at baseline, which could influence the effects of the training. To investigate the effect of piano training on cognitive and motor outcome measures and neuroplasticity, linear mixed models will be conducted in R using the lme4 package [92], with group, time and baseline measures as covariates variables. Statistical methods for handling missing data will be reported if required.

FreeSurfer [93] in FSL (FMRIB Software Library) will be used for the segmentation of grey matter ROIs. Tractography will be carried out on TOIs using MRTrix [94]. Linear mixed models will also be used to investigate relationships between cognitive ability and grey and white matter microstructure, measured using metrics of NODDI and SANDI at baseline and follow-up.

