## Method

### Participants, intervention, outcomes

#### Study setting

Cognitive and motor testing and MRI scanning will take place at CUBRIC before and after the 8-week intervention period, with data collection taking place between September 2024-July 2025. The intervention is self-guided, so the intervention will take place in participants’ homes.

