#### Outcome measures

Primary outcome measures are concerned with feasibility, measured in terms of recruitment, retention, acceptability and adherence (Table 1). Screening measures and secondary outcome measures concerning cognitive and motor performance are presented in Table 2. Secondary outcome measures concerning grey and white microstructure measurements are presented in Table 3.

**Table 1 Tab1:** Primary outcome measures: feasibility (recruitment, retention, acceptability and adherence)

Primary Outcome Measures: Feasibility
Feasibility will be assessed using the following measures: recruitment, retention, acceptability and adherence
1. *Recruitment* will be measured as the number of participants who are both deemed eligible for the study and who consent to taking part out of those who receive the participant information sheet. Reasons for ineligibility and declining to take part will be recorded in a screening log
2. *Retention* will be measured by the number of participants who complete the study after attending the follow-up visit after 8 weeks. Reasons for withdrawal and loss to follow-up will be recorded
3. *Acceptability* will be measured using a self-report questionnaire consisting of 27 Likert-scale assessing responses to the quality, difficulty level and content of the training and 4 qualitative questions on what could be improved in the training (Appendix C) 4. *Adherence* to the training will be measured by calculating frequency and duration of practice recorded in each participant’s practice diary. Participants are reminded weekly to record practice sessions as accurately as possible. The percentage of downloaded training videos will also be used as an indicator of the adherence to the technology used
The following predefined traffic lights system will determine feasibility success: green (all feasibility rates ≥ 70%) will indicate that the trial was successful; amber (no rates < 40%, but at least one < 70%) that the project requires review and design changes; and red (at least one rating < 40%) that the intervention and a future RCT are not feasible

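### The recruitment criterion is a conversion ratio under two conflicting denominators, so recruitment can be rated green after a large shortfall against the target of 50

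*Protocol article*

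**What the plan says.** The Primary objective names recruitment, with retention and adherence, as what the feasibility of a larger RCT rests on.

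The article defines the recruitment measure twice:

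- Statistical methods gives the percentage as "number of participants who provided consent/number of participants eligible".
- Table 1, item 1 (Outcome measures) counts those "who are both deemed eligible for the study and who consent to taking part out of those who receive the participant information sheet".

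Table 1 then applies cut-offs fixed in advance to the rates: "green (all feasibility rates ≥ 70%) will indicate that the trial was successful", and "red (at least one rating < 40%) that the intervention and a future RCT are not feasible". Amber lies between, with no rate below 40% and at least one below 70%.

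The target is in Sample size: "We plan to recruit 50 cognitively healthy individuals from the local area". That section also says the sample will hold the 95% margin of error for recruitment, retention and adherence to at most ±15 percentage points. Study setting gives the calendar, with "data collection taking place between September 2024-July 2025". Neither the target nor the calendar appears in the traffic light.

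**The concern.** A feasibility trial should tell the sponsor whether enough people can be enrolled in the time available, and whether those approached agree to join. These are separate questions, and the traffic light addresses only the second. A ratio of consenting to eligible people, or of consenting people to information-sheet recipients, takes the same value whether ten people join or fifty.

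The other inputs do not fill the gap. Retention is completers over consenters, adherence is logged practice over 40 days or 1,200 minutes, and acceptability comes from a questionnaire. None depends on reaching 50. Following the plan to the letter, the sponsor could declare a larger RCT feasible after a large shortfall. It could equally declare a fully recruited trial not feasible.

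The two denominators add a second difficulty: the colour for recruitment depends on which section the analyst follows.

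**Working it through.** **Inputs.** Recruitment formula: Statistical methods. Alternative definition and the 70% and 40% cut-offs: Table 1. Target of 50 and the ±15 points: Sample size. September 2024 to July 2025: Study setting. In the comparisons with the target, everyone who consents is assumed to be randomised.

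**1. The plan's own figure.** The worst-case 95% half-width is 1.96 × √(0.25/n). At n = 50 it is 1.96 × √0.005 = 13.9 points. The exact (Clopper-Pearson) interval extends at most 14.8 points from the estimate. The stated ±15 is therefore reproduced for a rate whose denominator is 50. The recruitment denominator is not 50 under either definition.

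**2. Green on recruitment with a shortfall (consented/eligible).**

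| Consented / eligible | Rate | Colour | Share of 50 |
|---|---|---|---|
| 7 / 10 | 70% | green | 14% |
| 14 / 20 | 70% | green | 28% |
| 20 / 25 | 80% | green | 40% |
| 34 / 48 | 70.8% | green | 68% |
| 35 / 50 | 70% | green | 70% |

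If fewer than 50 eligible people are found, the target cannot be met, yet the rate can still be 100%.

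**3. The converse.** With exactly 50 consenting:

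- 50/71 = 70.4%, green
- 50/72 = 69.4%, amber
- 50/125 = 40.0%, amber
- 50/126 = 39.7%, red

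A trial that meets its target is thus amber with 72 to 125 eligible people and red from 126.

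**4. The two denominators compared.** Take 20 consenting out of 25 eligible, which is 80% and green under Statistical methods. Under Table 1 the colour depends on how many people received the information sheet, a number the article does not give:

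- up to 28 sheets: green (20/28 = 71.4%)
- 29 to 50 sheets: amber (20/29 = 69.0%; 20/50 = 40.0%)
- 51 or more: red (20/51 = 39.2%)

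The same data can take any of the three colours. In each case the measure is still a ratio and does not register the count.

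**5. Precision after a shortfall.** The worst-case half-width is 14.9 points at n = 43, 15.1 at n = 42 and 21.9 at n = 20. These are maxima, reached at a rate of 50%. At n = 20 and higher rates:

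- 70%: 1.96 × √(0.21/20) = 20.1
- 80%: 1.96 × √(0.16/20) = 17.5
- 90%: 1.96 × √(0.09/20) = 13.1

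The guarantee that ±15 holds whatever the estimate is lost below 43 participants on this formula. At a high rate the actual interval may still be inside it.

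**6. Effect of a count-based rate.** With number randomised/50 on the same cut-offs, green needs at least 35 (0.70 × 50), amber is 20 to 34, and red is below 20 (0.40 × 50). Then 14 of 20 moves from green to red, and 20 of 25 and 34 of 48 move from green to amber.

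**The case against.** The strongest reply is that the plan never presents its recruitment rate as a measure of pace. The target of 50 is described as pragmatic and is not a progression criterion. A shortfall would be visible anyway through the screening log, the confidence intervals and CONSORT reporting for pilot trials. This stands in part: a low count would not be hidden. But the predefined rule would take no account of it, and the rule is what labels the larger trial feasible or not.

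Three stronger readings are tempting, and the article does not support them:

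- A reader might infer that volunteers answering adverts will nearly all consent once eligible, so that green is almost automatic. No consent rate is given, and there are plain reasons to decline: about 2.5 h of testing, about 30 min of MRI, 20 h of practice, or allocation to no training. The ratio does carry information on willingness to join. Its blindness to the count holds at any consent rate.
- A reader might treat September 2024 to July 2025 as an 11-month recruitment window. It is the data-collection period and includes follow-up after 8 weeks, which leaves roughly 9 months for enrolment. Twenty participants would be about 20/9 = 2.2 per month, not 20/11 = 1.8, and both are approximate.
- A reader might conclude that ±15 points is bound to be lost at n = 20. That is so in the worst case but not at a rate of 90%.

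It is also fair to object that a go/no-go threshold added now is not predefined. The protocol version is dated 20/10/2025, after the stated data-collection period. This stands and is met by labelling, as set out in the fix.

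**Conclusion.** The point holds. Under either definition the recruitment input to the traffic light is a conversion ratio that does not depend on the number enrolled. The two definitions also conflict. Under the Statistical methods formula, recruitment can be green at 28% or 40% of target, and a trial that reaches 50 can be amber or red. The cut-offs and formula are written out in the article, so this is not a detail left to an analysis plan.

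The conclusion is limited to the recruitment component. A reader might infer that a shortfall would produce an overall green. That also needs retention, adherence and acceptability at 70% or more, although none of these would register the shortfall. The eligible and consenting counts above are illustrations, and the article states no count-based threshold. Because the rule feeds a primary outcome and the remedy is cheap, the change should be made.

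**What to change.** - Choose one denominator for the conversion ratio, state it identically in Table 1 and Statistical methods, and report the result as a conversion figure.
- Add a second recruitment rate in both places: 100 × (number randomised by the last date that allows the 8-week follow-up within the data-collection period / 50), judged on the existing 70% and 40% cut-offs.
- Report the number randomised per month of actual enrolment.
- State that this criterion was added at the protocol version in which it first appears, since the current version already postdates the stated data-collection period.

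The cost is one formula using counts the trial needs to hold anyway. The light may be less favourable, and the added criterion cannot be presented as fully predefined. Applying 70% and 40% to the count reuses the article's own cut-offs, but it is a choice that the sponsor should state as such.
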